# PICO

P- Children aged 24.0 -59.9 months in southern Ethiopia, Tulla sub city, with mild and moderate anemia

I - Daily feeding of 150g bread containing 70 mass % amaranth grain and 30 mass % mashed chickpea

C -Daily feeding of 150g bread containing 100% maize

O- Change in hemoglobin level, change in ferritin status, changes in anthropometric status.

The research questions will be answered in three subsequent papers and the general and specific objectives are given below for the three papers.

## General objective one

To estimate the prevalence of iron deficiency anemia in children age 24.0-59.9 month in Tulla sub city, South Ethiopia.

**Specific objective**

1. To describe the distribution of hemoglobin levels among children 24.0-59.9 months of age in Tulla sub-city South Ethiopia including mean, median, ranges and 95 % confidence intervals (95% CI) and percentage of children falling under the category of mild and moderate anemia.
2. To describe the distribution of ferittin levels of children 24.0-59.9 months of age in Tulla sub city south Ethiopia including mean, median, ranges and 95 % confidence intervals (95% CI) and determine the percentage of children who are mild- and moderate anemic with low ferritin levels.
3. To describe the anthropometric indices of children 24-59 month of age in Tulla sub city south Ethiopia
4. To assess amaranth acceptability and policy direction in Tulla sub city south Ethiopia.

## General objective two

To evaluate if feeding children with either 150gm bread containing 70mass% amaranth grain and 30mass% chickpea per day for 6 month will increase the hemoglobin level of mild and moderate anemic children 24.0 up to59.9 months of age by 0.7g/dl compared with children in equivalent amount of 100% maize bread in Tulla sub city south Ethiopia .

**Specific objective**

1. To compare the hemoglobin values in children receiving amaranth grain containing bread and children receiving maize bread in Tulla sub city South Ethiopia.
2. To compare the ferritin values in children receiving amaranth grain containing bread with children receiving maize bread in Tulla sub city south Ethiopia.
3. To compare the anthropometry indices in children receiving amaranth grain containing bread with children receiving maize bread in Tulla sub city south Ethiopia.
4. To compare incidence of childhood illness in children receiving amaranth grain containing bread with children maize bread in Tulla sub city south Ethiopia.
5. To compare cost effectiveness of amaranth containing bread on the prevention of iron deficiency anemia in Tulla sub city south Ethiopia
6. To compare compliance and adherence of mother between amaranth containing bread and maize bread groups.

# Method

## 4.1. Study Area

Ethiopia is a large, country in Eastern Africa with a population of over 90 millions. More than 80% of its population live in the countryside and make their living through traditional agricultural practices. The proposed research will be conducted in the southern part of Ethiopia in Hawassa city administration, Tulla sub city. The city is located 270 km from Addis Abeba, the capital city of Ethiopia. Currently Hawassa city consists of 8 sub cities and 32 villages/Kebelles each having its own administration offices.Tulla sub citiy is on e of the sub city of Hawassa city administration. Most part of the Tulla sub city is rural, the current projected total population of Hawassa city is 328 thousand, of this 169 thousand are males and 159 thousand are females. The estimated numbers of the households are 70 thousand. 51 thousand are children under five years. 46 thousand are aged 24-59 months. Annual average temperature is 12-27^0^C and the annual average rain fall is 500-1800 mm. The main crops produced in the area that maize, hallicot beans and Irish potatos. Amaranth is growing as a wild plant in most areas of Tulla sub city and the leave part is used by the community as a vegetable.

## Study population

The source population of this study will be children aged 24-59 months of age residing in Tulla sub-city of Hawassa city administration. Tulla sub city is divided in to 8 kebelles. From this kebelle Cheffe cote jebesa and Gara riketa will be purposively select for the project site because they are near to the city, has transport accesses and amaranth grows widely in the area as wild plant.

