## **2.1. Research questions**:

1. What is the prevalence of iron deficiency anemia defined as Hemoglobin below 11mg/dl and serum ferritin below 12µg/L among children from 24.0 to 59.9 months of age in southern Ethiopia?
2. Does consumption of 150 mg bread daily containing 70 mass percentage amaranth grain increases mean hemoglobin level by 0.7mg/dl among children 24.0-59.9 months of age compared to equivalent amount of 100 percent maize bread in southern Ethiopia?
3. Is Amaranth grain culturally acceptable and how is the policy direction towards amaranth grain to use as staple food in Ethiopia?

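### The survey's stated target is Tulla sub-city (and southern Ethiopia), but only two purposively chosen kebeles of eight are sampled, so its 95% intervals have no guaranteed coverage beyond those two

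*Protocol*

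**What the plan says.** **Target.** Protocol section 2.1 (Research questions) asks in its first question for the prevalence of iron deficiency anemia "among children from 24.0 to 59.9 months of age in southern Ethiopia". General objective one is narrower: "To estimate the prevalence of iron deficiency anemia in children age 24.0-59.9 month in Tulla sub city, South Ethiopia". The first two specific objectives under it describe hemoglobin and ferritin in Tulla, the first of them "including mean, median, ranges and 95 % confidence intervals (95% CI) and percentage of children falling under the category of mild and moderate anemia". The third describes anthropometry in Tulla. The section Study population says: "The source population of this study will be children aged 24-59 months of age residing in Tulla sub-city of Hawassa city administration".

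**What is sampled.** The same section says that Tulla has eight kebeles and names two that "will be purposively select for the project site because they are near to the city". It adds two further reasons: transport access, and amaranth growing widely there as a wild plant. Sampling Technique registers children in the selected kebeles only and takes 340 of them by simple random selection. Figure 3 repeats that the research area is chosen purposively.

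**Size.** Sample Size gives 340 for the survey. It cites 33% mild and moderate anemia in south Ethiopia, a precision printed as 0.5, 95% confidence and the need for 100 trial participants.

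The Protocol states no random choice of kebeles, no weighting and no limit on how far the survey result may be generalised.

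**The concern.** The population that the objectives describe is not the population from which children are drawn. Random selection within two kebeles supports inference to those two kebeles. It does not support inference to the other six, whose children have no chance of selection, and still less to a region.

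The choice could matter on the Protocol's own account. Section 4.1 (Study Area) says most of Tulla is rural, while nearness to the city and transport access are two of the three selection reasons. The Introduction and the Statement of the problem link anemia to low socio-economic status, list low family income as a predictor of iron deficiency anemia, and say that animal products are eaten especially little in rural areas.

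At stake is the survey's main answer. Prevalence is the first research question and a general objective, and the study is meant to inform policy makers. Carried out as written, it would report a figure for Tulla with an interval that reflects only sampling error within two of its kebeles.

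**Working it through.** **1. Reproduce the survey size.** Inputs from Sample Size: p = 0.33, 95% confidence (z = 1.96). Formula for one proportion under simple random sampling: n = z² p(1 − p) / d².
- With d = 0.05: 1.96² × 0.33 × 0.67 / 0.05² = 339.7, rounded up to 340. This is the Protocol's figure.
- With d = 0.5 as printed: 3.4, rounded up to 4. This does not give 340, so 0.5 is read here as a slip for 0.05.

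**2. Precision that this size buys.** Standard error = √(0.33 × 0.67 / 340) = 0.0255. Half-width = 1.96 × 0.0255 = 0.050, or 5.0 points. The formula assumes that every child in the target population can be drawn with equal chance. That is true of the registered children in the two kebeles and untrue of Tulla. The 33% is for mild and moderate anemia. Iron deficiency anemia, which also requires low ferritin, is a narrower condition whose prevalence is not given, so the 5.0 points describe anemia and not the exact quantity in research question 1.

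**3. What happens to coverage for Tulla.** The documents give no kebele-level prevalence, so this step is an illustration on assumed values: eight kebeles of equal size, the two sampled ones at 33%, and the other six differing from them by D points in the same direction.
- Tulla prevalence = (2 × 33 + 6 × (33 + D)) / 8 = 33 + 0.75 D, so the survey is off by 0.75 D.
- With bias b = 0.75 D and standard error s = 0.0255, both as proportions, coverage = Φ(1.96 − b/s) − Φ(−1.96 − b/s).

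| D (points) | Bias (points) | Coverage of the nominal 95% interval for Tulla |
|---|---|---|
| 0 | 0 | 95% |
| 3 | 2.25 | 86% |
| 5 | 3.75 | 69% |
| 10 | 7.5 | 16% |

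The nominal level is reached only when the kebeles are alike. A larger sample from the same two kebeles would not help: the bias stays the same and the interval narrows around the wrong value.

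**The case against.** **The site choice is openly stated, and the survey is also the trial's recruitment frame.** Both are true, and Sample Size cites the need for 100 trial participants. For the two kebeles, simple random selection of 340 is sound and needs no design effect. But disclosing the choice does not widen what the interval covers, and the objectives still name Tulla.

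**Southern Ethiopia is partly a locator.** This largely stands. Research question 2, on the trial, uses the same phrase, and the PICO section writes it together with Tulla. A reader might infer a claim to estimate regional prevalence; the wording permits that but does not require it. The mismatch with Tulla does not depend on it, because Study population makes all Tulla children the source population.

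**The intervals are less explicit than they seem.** The specific objectives attach 95% intervals to the hemoglobin and ferritin descriptions, Statistical methods speaks of means and percentages, and no sentence expressly promises an interval for iron deficiency anemia prevalence. This stands as a detail. The described distributions are still those of Tulla children, and the survey size uses 95% confidence.

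**Stronger readings that the Protocol does not support.**
- A reader might take local eating of amaranth leaves as a reason for choosing the kebeles. It is not. Section 4.1 only describes the area when it says "the leave part is used by the community as a vegetable", and it says amaranth grows wild in most of Tulla, so abundance may separate the two kebeles from the rest less than city access does.
- A reader might apply a design effect with an assumed intracluster correlation and call the result the true half-width. That model treats kebeles as drawn at random from a large population. Here they were picked on purpose, and Tulla has only eight.
- A reader might infer that the survey is biased in a known direction. No kebele-level figures are given, and the interval could still contain the Tulla value.

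**Conclusion.** The mismatch is real and lies in the Protocol's own text: the target is Tulla sub-city, while the frame is two purposively chosen kebeles of eight. The half-width of about 5 points at 33% anemia holds for those two kebeles, if 0.05 is the intended precision. For Tulla or southern Ethiopia the 95% intervals have no guaranteed coverage. How far they fall short is unknown; the 69% and 16% at differences of 5 and 10 points rest on assumed equal kebele sizes and assumed differences, and show scale only.

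The point concerns the survey alone. It should not be read as a weakness in the trial's internal validity: children are randomised 1:1 with stratification by kebele, so the comparison of breads is not affected. The change is worth making because it alters what the survey can conclude and costs almost nothing.

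**What to change.** - Restate research question 1, general objective one and its survey objectives on hemoglobin, ferritin and anthropometry as applying to children in the two selected kebeles. Change the source population for the survey to match.
- Keep Tulla sub-city and southern Ethiopia only to say where the kebeles lie.
- Add one sentence saying that the 95% intervals apply to those two kebeles, and that extending them to Tulla would rest on an untested assumption that the other six are alike.

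**Cost.** Wording only, with no change to the survey size, recruitment or the trial. The downside is a narrower stated population. When these sentences are rewritten, the age range needs checking as a separate matter: Sampling Technique registers children up to 54.0 months, against 59.9 in the objectives.

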## Study period

The proposed study period will be from month 12 2016 to month 3 2017.

- 1. Study subject 24.0 months – 59.9 months of age child who live in Tulla sub city southern Ethiopia.

## Sample Size

The base line data (survey part) will be used as a basis for the trial part. After completing the survey part the trial sample will be recruited from the survey study participants, in this way the survey will be providing the baseline data for the trial. The survey sample size will be 340 considering a need for 100 trial participants, 33% of mild and moderate anemia prevalence in south Ethiopia, 0.5 degree of precision and 95% confidence intervals. The survey sample size may be increased till the numbers of eligible individuals are identified for the trial if anemia is less prevalent than 33%.

The sample size of the trial is calculated by using Stata I.C. 14 software using the sample size command, considering 0.7 mean difference,1 standard deviation, power 90% and attrition rate 12% the total sample size will be 99 (100) in the two groups. The total sample will be divided in to the amarnth70%/chickpea30% versus the maize 100% groups. Thus it will be 50 in the amaranth/chickpea group and 50 in the maize group ([2](#_ENREF_2)).

## Participants

The target population of this study is children 24.0-59.9 months of age with mild and moderate anemia in Tulla sub-city, southern Ethiopia. Below is described the inclusion and exclusion criteria of the trial participants.

## Inclusion criteria

- Children 24 months up to 59 months
- Children with hemoglobin level 7 to <11 mg/dl
- Currently residing in the study area, Tulla sub-city of Hawassa city administration, having lived in the study area for at least 6 month prior to the study and who are planning to continue to be there for the next 1 year.
- Guardians provide informed consent and the children ascent.

## Exclusion criteria

- Children with chronic illness like HIVAIDS, tuberculosis, cancer and any other unspecified chronic illness
- Severely malnourished children < -3 Z score
- Children who are taking iron supplements
- Children who got a blood transfusion in the last 6 months
- Children who are unable to collaborate (any somatic or mental disability making collaboration difficult more than expected for the age range)
- Children with repeated malaria who are diagnosed as positive for malaria at least 3 times the last 3 months
- Any suspected hematological disease

## Sampling Technique

All children age 24.0-54.0 months will be registered in the selected Kebelles. From the registered children 340 children will be select by using simple random selection for survey part.

After assessing Hgb, 100 children with mild and moderate anemia status will be included in the trial. The included children will be allocated randomly 1:1 to amaranth70% chickpea30% versus maize100% 150g daily bread. Single randomization stratified by Kebelle will be used.

Randomization will be done using random org sequence free soft ware. Researchers not involved in the field work in Hawassa University will provide the sequence; researchers at the partner institution UiB will provide the seed number.

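### The survey register stops at 54.0 months although objectives, target population and eligibility run to 59 or 59.9 months; secondarily, the survey precision is misprinted as 0.5

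*Protocol*

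**What the plan says.** **Age range.** Protocol, Sampling Technique: "All children age 24.0-54.0 months will be registered in the selected Kebelles". The 340 survey children are then drawn by simple random selection from those registered, and the trial children come from the survey. Elsewhere the range is wider:

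- General objective one: "To estimate the prevalence of iron deficiency anemia in children age 24.0-59.9 month in Tulla sub city".
- Participants: "The target population of this study is children 24.0-59.9 months of age with mild and moderate anemia".
- Inclusion criteria: "Children 24 months up to 59 months".
- The Summary, Aim, Research questions, Hypothesis, PICO, General objective two and the study-subject line under Study period all end at 59.9 months.

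**Survey size.** Protocol, Sample Size: "The survey sample size will be 340 considering a need for 100 trial participants", with the further inputs "33% of mild and moderate anemia prevalence in south Ethiopia, 0.5 degree of precision and 95% confidence intervals".

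**Extension.** The same section lets the survey grow "till the numbers of eligible individuals are identified for the trial if anemia is less prevalent than 33" per cent.

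**The concern.** Sampling Technique is the instruction that field staff follow when they build the register. If it is applied literally, children aged above 54.0 and up to 59.9 months are never listed and cannot be selected. Prevalence would still be reported for 24.0-59.9 months and the trial population described in the same terms. Analysis cannot repair this, because nothing would have been measured in the missing age band.

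The survey-size paragraph has two lesser faults. Its printed precision does not lead to its printed size. Its extension rule is tied to low prevalence, whereas what the trial needs is a number of eligible children whose guardians consent. At stake there is whether a reader can reproduce 340, and whether staff know they may continue if the shortfall has another cause.

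**Working it through.** **1. Age range.** Inputs: 24.0-54.0 months (Sampling Technique) and 24.0-59.9 months (Participants, General objective one).

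- Target span: 59.9 − 24.0 = 35.9 months.
- Omitted span: 59.9 − 54.0 = 5.9 months.
- Share omitted: 5.9 / 35.9 = 0.164, about 16%, assuming ages are spread evenly. The protocol gives no age distribution.

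Effect on the prevalence estimate: if the omitted children make up 0.164 of the target, the error is 0.164 × (prevalence at 24.0-54.0 months − prevalence above 54.0 months). Each percentage point of difference between the age bands shifts the estimate by about 0.16 points. To equal a planned half-width of 5 points, the bands would have to differ by 0.05 / 0.164 = 0.30, or 30 points. The protocol gives no prevalence by age, so the actual shift is unknown.

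**2. Survey size.** Inputs from Sample Size: p = 0.33 and 95% confidence (z = 1.96). Formula: n = z² p(1 − p) / d².

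| Precision d | n | Rounded up |
|---|---|---|
| 0.05 | 339.7 | 340, the protocol's figure |
| 0.5, as printed | 3.4 | 4 |

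So 340 is reproduced exactly with d = 0.05. Conversely, at n = 340 and p = 0.33 the half-width is 0.04998.

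**3. Yield for the trial.** Expected children with mild or moderate anemia: 340 × 0.33 = 112.2. The number expected to remain equals 100 when the combined loss is 1 − 100/112.2 = 10.9%. Put another way, the eligible fraction of those surveyed must be at least 100/340 = 29.4%.

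The protocol states no exclusion or refusal rate, so the 10% and 20% losses below are assumptions. The probabilities are exact binomial.

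| Combined loss after hemoglobin screen | Expected eligible | P(at least 100 from 340) | Surveyed for an expected 100 |
|---|---|---|---|
| 0% | 112.2 | 0.93 | 304 |
| 10% | 101.0 | 0.57 | 337 |
| 20% | 89.8 | 0.12 | 379 |

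**4. The trigger against the need.** At 33% prevalence with a loss above 10.9%, a shortfall is expected but the stated condition is not met. At a prevalence between 29.4% and 33%, the condition is met although 340 children would still give an expected 100 before losses. Prevalence is therefore a poor proxy for the quantity that matters.

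**The case against.** **The age limit may be a slip.** The figure 54.0 occurs once, against 59 or 59.9 everywhere else, so a misprint is likely. That explains the error but does not remove it, because the one place where it occurs is the registration instruction. One could also argue that 54.0 was deliberate, since 54.0 months plus 6 months of feeding is 60.0. The protocol gives no such reason, its inclusion criteria admit older children, and the survey has no feeding period that would call for the limit.

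**The trial result is unaffected.** This stands. Children are randomised from a common register, so the hemoglobin comparison keeps its validity. What suffers is survey coverage and the population to which both results apply.

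**The survey size is sound.** This also stands. A reader might infer from the printed 0.5 that 340 has no basis. In fact 340 is exactly the size for 0.05 at 33% prevalence. A reader might also infer that 340 cannot supply 100 trial children. At the protocol's own prevalence it yields about 112, with a 93% chance of at least 100 before losses.

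**The extension clause already aims at eligible children.** It does, and it does not say that low prevalence is the only ground for continuing. Consent appears in Table 4 in Month 2, alongside the survey, so some refusals may occur before the 112 are counted. On the other hand, the section on individual advantage and disadvantage foresees families declining after diagnosis. What remains is narrow: the stated condition names low prevalence and is silent on exclusions and refusals.

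**Conclusion.** The age contradiction holds and is the main point. As written, the register omits children above 54.0 months, about 16% of the target range under an even age distribution, and the prevalence estimate would not cover its stated population. How far the estimate would move cannot be said from the protocol; by the arithmetic above it would be small unless the oldest children differ markedly.

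The precision is a decimal error, and no planned number changes.

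The extension wording is a minor weakness. Even with an assumed 20% loss and no extension, about 90 children would be randomised. After the protocol's 12% attrition, 90 × 0.88 = 79 remain, about 39.6 per arm, and power is about 87% against the planned 90%. A reader might infer a serious threat to power, but this figure and the absence of any stated loss rate do not support that. A reader might also try to size the loss from the national severe-stunting figure in the Background. That figure describes all Ethiopian children under five, not anemic children in the two chosen kebelles, and the exclusion criterion for severe malnutrition does not say that it refers to height-for-age.

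**What to change.** 1. In Sampling Technique, change 24.0-54.0 to 24.0-59.9 months. This must be done before the census, which Table 4 places in Month 2. It costs one wording change and a somewhat longer register; the number surveyed is unchanged.
2. In Sample Size, change the precision from 0.5 to 0.05 (5 percentage points) and keep 340. This costs nothing.
3. In the same section, let random selection continue until 100 eligible, consenting children are identified, whatever the cause of the shortfall, in place of the condition on prevalence below 33%. The cost is possibly some extra survey visits, which the protocol already allows in the low-prevalence case. For scale, about 379 children would be surveyed for an expected 100 if the loss were 20%, against 340 planned.
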